## Methods

### Overview

Auto-ML will be built atop current big data software, enabling it to operate on one computer or a cluster. Built atop the Hadoop distributed file system, Spark [78] is a major open source software system supporting MapReduce [76] for distributed computing. Spark has an accompanying machine learning library, MLlib [79]. Spark is able to perform machine learning more than 100 times quicker than Hadoop [80]. Auto-ML will be built using the Spark package as well as novel techniques to address the current software’s limitations.

### Aim 1

#### Overview

Our first aim is to finish developing Auto-ML to automate model selection for machine learning with clinical big data and validate Auto-ML on seven benchmark modeling problems of clinical importance.

Figure 1 compares Auto-ML’s approach of constructing models to the present one. Four steps are carried out sequentially during machine learning: temporally aggregate clinical attributes; choose hyper-parameter values, feature selection techniques, and algorithms; construct models; and assess models. The temporal aggregation step is optional (eg, when no repeatedly recorded attribute exists). Auto-ML will use Spark as the basis for distributed computing. Auto-ML will be coded in Java so it can use the open source software systems Spark and Weka, which all have a Java application programming interface and/or are coded in Java. The user will specify the storage location of the dataset in Auto-ML’s graphical input interface. Auto-ML will then put the dataset into Spark prior to analysis.

**Figure 1 figure1:**
[figure not shown]
Auto-ML’s approach of constructing machine learning models versus the present one.

**Figure 2 figure2:**
[figure not shown]
Progressive sampling adopted in our draft automatic model selection method.

#### Auto-ML’s Machine Learning Functions

Auto-ML will integrate MLlib [79] and Weka’s [19] machine learning functions by altering source code and/or invoking the Java application programming interfaces. As a broadly used machine learning tool kit, Weka includes many popular feature selection techniques and learning algorithms. distributedWekaSpark [81] is the distributed computing package of Weka for Spark that is able to operate on a computer cluster. MLlib is a distributed machine learning library in Spark implementing some techniques and algorithms supported by Weka. Auto-ML will support all techniques and algorithms available in Weka. Whenever possible, Auto-ML will use MLlib’s code, which fuses with Spark better than distributedWekaSpark’s code [81].

Weka’s [19] graphical user interface covers feature selection (optional), model construction, and model assessment. In the input interface, the Weka user designates the dependent variable, independent variables, data file, learning algorithm, and the hyper-parameter values of the algorithm. After the user clicks the start button, Weka constructs a model and shows its performance measures. For machine learning, Auto-ML’s graphical user interface will work similarly with two main differences. First, in Weka, the user must specify an algorithm prior to model building. Like Auto-WEKA [25], Auto-ML will use a hyper-parameter to represent the option of feature selection technique and automatically select the hyper-parameter values, technique, and algorithm. The user may override the choice of Auto-ML. Second, to facilitate the user in tracking the automatic selection’s progress, Auto-ML shows a curve presenting the highest accuracy reached over time. The user can terminate the process at any moment and obtain the most accurate model built. In the following sections, we outline the main techniques that we will use to build Auto-ML.

### Aim 1 (a)

#### Overview

For Aim 1 (a), we aim to devise a method to efficiently and automatically choose hyper-parameter values, feature selection techniques, and algorithms. Our review paper [26] showed that few automatic selection methods [25,28-31,82] have been fully implemented and can manage an arbitrary number of combinations of hyper-parameter values and many learning algorithms. All of these methods are similar to or based on the Auto-WEKA automatic selection approach [25], yet none of them can efficiently handle large datasets. To overcome the current methods’ inefficiencies, we drafted a method based on Bayesian optimization for response surface to rapidly identify, for a specific modeling problem, a good combination of hyper-parameter values, a feature selection technique, and a learning algorithm when a large number of algorithms and techniques are examined [35,83]. The method represents the option of technique as a special hyper-parameter; proceeds in stages; and conducts progressive sampling [84], filtering, as well as fine-tuning to rapidly shrink the search space. We conduct fast trials on a small sample taken from the dataset to drop unpromising combinations early, reserving resources to fine-tune promising ones. A combination is promising when a model built using the combination and the sample reaches an error rate below a beginning threshold. Then, we decrease the threshold, enlarge the sample, test and adjust combinations, and cut the search space several times. At the last stage, we find an effective combination using the full dataset.

More specifically, at each stage our method uses a training sample and a validation sample. They have no overlap and contain data instances randomly chosen from the dataset. We keep the validation sample the same and expand the training sample across stages (see Figure 2). At the first stage, we start from a small training sample. For each learning algorithm, we evaluate a fixed number of random hyper-parameter value combinations, if any, as well as its default one. To evaluate a combination, we use the combination, the training sample, and algorithm to construct a model, then use the validation sample to assess the model’s error rate. We identify and remove unpromising algorithms based on the test results. At each subsequent stage that is not the last one, we enlarge the training sample. For each remaining algorithm, we construct a separate regression model, use a Bayesian optimization for response surface approach to choose several new hyper-parameter value combinations, and test these combinations. We identify and remove additional unpromising algorithms based on the test results. At the last stage, we do some final tests on the full dataset to come up with the ultimate search result.

Our draft method needs further optimization for efficiency and effectiveness. To do this, we will expand the draft method to include multiple optimization techniques: the seven outlined in our design paper [24] and the six described in the following sections.

#### Technique 1

In Technique 1, we will use two validation samples to help avoid overfitting. At each stage except for the last one, our draft method [35,83] uses the same validation sample containing a moderate number of data instances to perform many tests. This could lead to overfitting to the validation sample [20-23] that will misguide future search. To help avoid overfitting, we will use two validation samples of equal size with as little overlap as possible, and reduce the frequency of revealing information about the second validation sample [23]. When the dataset has enough data instances, the two validation samples will have no overlap. For a combination of hyper-parameter values and a learning algorithm, we use the combination and the training sample to construct a model and assess the model’s error rate twice, once on either validation sample. Intuitively, the two error rates would be roughly the same in the absence of overfitting. If the error rate on the first validation sample is higher than a specific threshold (eg, in the top 50% of the error rates on the first validation sample of all combinations tested so far at this stage), we use it as the combination’s error rate estimate. Regardless of its exact value, a high error rate estimate will guide future search to avoid the combination’s neighborhood. If the threshold is not exceeded, we compare the error rate on the first validation sample with that on the second. If the former is not lower than the latter by a certain threshold (eg, 5%), we use the former as the combination’s error rate estimate. Otherwise, we use the latter as the combination’s error rate estimate, as overfitting to the first validation sample is likely to have occurred.

The above approach uses the same two validation samples across different stages. Alternatively, if the dataset contains many data instances, we can use a different validation sample at each stage. Each time we arrive at a new stage, we redo sampling to obtain a new validation sample. This also helps avoid overfitting to the same validation sample that is repeatedly used. We will compare the two approaches and choose the one that performs better.

#### Technique 2

In Technique 2, we will use multiple feature selection techniques concurrently to drop unpromising features early. Feature selection and model building time rises proportionally to the number of features at a minimum. Doing a test is slow when many features exist in the dataset. To tackle this issue, we previously proposed that before doing tests, we apply a feature selection technique to the dataset, or a large sample of it, and rapidly drop features not likely to have high predictive power [24]. Yet, like the “no free lunch” theorem [85] shows, no technique can guarantee good performance in all cases. Relying on a single technique can be risky, causing predictive features to be dropped erroneously. To reduce the risk, we will use multiple techniques concurrently. A feature is dropped only if at least a certain number of these techniques all regard it as unpromising.

#### Technique 3

In Technique 3, at the first stage for each learning algorithm, we will ensure a minimum number of tests conducted on every feature evaluator and feature search method. Every feature selection technique adopts a feature evaluator as well as a feature search method [25]. At the first stage for no learning algorithm, our draft method guarantees the number of tests conducted on every feature evaluator or feature search method. Without enough tests, we cannot tell how well a feature evaluator or feature search method works with the algorithm. To tackle this issue, at the first stage for each algorithm, we will check the number of tests conducted on every feature evaluator and feature search method. If the number for a feature evaluator or feature search method is smaller than a specific threshold (eg, 3), we will conduct more tests for the feature evaluator or feature search method to make up the difference. This approach can be adopted for several other components of a data analytic pipeline [86], such as handling imbalanced classes and missing values.

#### Technique 4

In Technique 4, we will share information on the best few results obtained so far among different learning algorithms. Our draft method conducts a separate set of tests for every algorithm. When conducting tests for an algorithm, we may find a combination of a feature selection technique and its hyper-parameter values with superior performance. Yet, the combination may not be tested together with other algorithms, as its information is not shared with them. This can degrade the ultimate search result’s quality. To tackle this issue, we will share information on the best few results obtained so far among different algorithms. At the end of each stage except for the last one, we will identify a prechosen number *n*_1_ (eg, 3) of combinations of algorithms, techniques, and hyper-parameter values that achieve the lowest error rates among all combinations examined so far. Then we will extract the corresponding *n*_2_ combinations of techniques and their hyper-parameter values. Typically, *n*_2_ is equal to *n*_1_. Occasionally, *n*_2_ can be smaller than *n*_1_, as the same combination of a technique and its hyper-parameter values may appear in more than one of the *n*_1_ combinations. At the next stage, for each remaining algorithm, we ensure each of the *n*_2_ combinations of techniques and their hyper-parameter values is tested by adding additional tests, if needed.

#### Technique 5

In Technique 5, for a dataset with relatively few data instances, we will dynamically allocate its data instances between the training and validation samples across stages. A dataset with relatively few data instances can still be large if it contains many features. In this case, our draft method uses a fixed portion of the dataset as the validation sample, which includes a small number of data instances. Because of insufficient testing, the error rate estimates obtained on the trained models can be nonrobust, degrading the ultimate search result’s quality. To tackle this issue, we will dynamically allocate the data instances in the dataset between the training and validation samples across stages. At each stage except for the last one, we give all data instances that are in the dataset, but not in the training sample, to the validation sample. With more data instances in the validation sample, the error rate estimates obtained on the trained models can be more robust. Krueger et al [87] used a similar approach to perform fast cross-validation to select a good hyper-parameter value combination for a given learning algorithm and modeling problem.

#### Technique 6

In Technique 6, we will consider distances between hyper-parameter value combinations when choosing randomly sampled combinations for testing. At each stage that is neither the first nor the final one, for each remaining learning algorithm, our draft method performs one or more rounds of Bayesian optimization. In each round, several new and randomly sampled combinations are chosen out of many for testing and used to adjust the regression model. For the regression model to guide search well, the combinations chosen for testing need to have a reasonable coverage of the hyper-parameter space rather than all reside in a small region. To achieve this, we will attempt to ensure that each randomly sampled combination chosen for testing is separated from each other combination chosen for testing by at least a specific distance. The distance threshold may decrease over stages.

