##### Model Information

The dependent variable is whether a patient had a diagnosis of type 2 diabetes in the following year. Two-thirds of patients will be randomly selected and put into the training set to construct models. The remaining one-third of patients will form the test set for assessing model performance. We will use the area under the receiver operating characteristic curve (AUC) [19] performance metric.

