##### Model Information

The dependent variable is whether an asthmatic patient incurred hospital use—inpatient stay or ED visit—with a primary diagnosis of asthma (ie, ICD-9 493.xx or ICD-10 J45/J46.*) in the following year [14,63,64]. As outcomes need to be computed for the following year, we effectively have 11 years of IH data. We will construct models using the data in the first 10 years and acquire a model’s accuracy estimate via testing on the data in the 11th year. This mirrors future use of the model in practice. We will use the AUC [19] performance metric.

#### Modeling Problem 9

Modeling Problem 9 involves using UWM’s incomplete data to predict individual diabetic adults’ costs in the next year.

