##### Model Information

The dependent variable is a diabetic patient’s total allowed cost to UWM in the following year [60,61]. Allowed costs are less inflated than billed costs and less subject to variation due to member cost sharing than net incurred claims [60]. We will adopt the medical consumer price index [105] to convert all costs to 2016 US dollars to handle inflation. As outcomes need to be computed for the following year, we effectively have 4 years of UWM data. We will construct models using the data in the first 3 years, and acquire a model’s accuracy estimate via testing on the data in the 4th year. This mirrors future use of the model in practice. We will use the *R*^2^ performance metric [61].

To fill the scope gap mentioned in the introduction, we will use a constraint to find patients who tend to get most of their care at UWM. Intuitively, it is easier to identify future high-cost patients among them than among others. We will use UWM’s incomplete data to build a cost prediction model and apply it to them. Regardless of his/her total future cost at non-UWM facilities, a patient who will incur high cost at UWM can be a candidate for care management. By care managing future high-cost patients identified by the model, we will expand the scope of using care management to improve outcomes. The principle of our approach to using incomplete data generalizes to many other clinical applications.

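### The Auto-ML search rules are written in terms of error rate, but Problems 1 and 8 are judged on AUC and Problem 9 on R-squared; the search loss should be tied to each problem's own metric

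*Protocol article*

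**What the plan says.** Protocol article, Aim 1 (a), Overview, describes a staged search. It sets the entry rule as "A combination is promising when a model built using the combination and the sample reaches an error rate below a beginning threshold". Each candidate is built on the training sample, and the team will "then use the validation sample to assess the model’s error rate". After each early stage, "We identify and remove unpromising algorithms based on the test results".

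Two of the planned improvements keep the same criterion. Technique 1, the guard against overfitting, will "assess the model’s error rate twice, once on either validation sample" and compares the two values using an example 5% margin. Technique 4 passes on to the other algorithms the settings "that achieve the lowest error rates among all combinations examined so far".

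The evaluation metrics are set elsewhere:
- Modeling Problem 1, Model Information: "We will use the area under the receiver operating characteristic curve (AUC) [19] performance metric".
- Modeling Problems 2-7: multi-class accuracy.
- Modeling Problem 8, Model Information: "We will use the AUC [19] performance metric".
- Modeling Problem 9, Model Information: R-squared, for next-year allowed cost in dollars.

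No section says that the search criterion follows the metric of the problem in hand. The Results section reports the past performance of the same draft method as a reduction in classification error rate. That is the article's only gloss on the term.

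**The concern.** A search finds models that are good on the quantity it ranks by. Error rate is measured at one cut-off and is dominated by the larger class; AUC measures ranking over all cut-offs. When events are a minority, models with clearly different AUCs can have nearly the same error rate. A stage rule based on error rate may then remove an algorithm that would have done better on AUC. For a continuous cost, a 0/1 error rate has no meaning, so the stated rule gives no criterion for Problem 9.

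At stake are the two Aim 2 hypotheses (an AUC gain of at least .05 in Problem 8 and an R-squared gain of at least 5% in Problem 9) and Problem 1's share of the Aim 1 (d) hypothesis that at least 60% of researchers reach 95% of the gold standard. The Aim 1 (d) results also supply the probability *p*1 used in the Aim 3 simulations. The user may override Auto-ML's choice, but participants are recruited for having limited machine learning knowledge, so this is a weak safeguard.

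**Working it through.** The article gives no figure for this point, so there is nothing to reproduce. The check sets criterion against metric, then asks how much error rate says about AUC.

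**1. Criterion against metric**

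| Problem | Search criterion as written | Metric used to judge the model | Match? |
|---|---|---|---|
| 1 | error rate | AUC | no |
| 2-7 | error rate | accuracy (1 minus error rate) | yes |
| 8 | error rate | AUC | no |
| 9 | error rate | R-squared, continuous cost | 0/1 error rate undefined |

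**2. Problem 1, equal variances.** The event rate comes from the Problem 1 dataset description: p = 1904/9948 = 0.1914. Assumption: scores are binormal with equal variances, cut at the point that minimises error.
- Separation: d = √2 · Φ⁻¹(AUC)
- Best cut-off: t = d/2 + ln((1−p)/p)/d
- Lowest error = (1−p)·[1−Φ(t)] + p·Φ(t−d)

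For AUC .75: d = 0.954, and ln(0.8086/0.1914) = 1.441, so t = 0.477 + 1.441/0.954 = 1.988. The false-positive rate is 0.0234 and the false-negative rate 0.849. Error = 0.8086 × 0.0234 + 0.1914 × 0.849 = 0.0189 + 0.1626 = 0.1815.

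| AUC | .60 | .70 | .75 | .80 | .85 |
|---|---|---|---|---|---|
| Lowest error | 19.14% | 18.87% | 18.15% | 16.86% | 14.94% |

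Predicting no diabetes for everyone gives 19.14% with AUC .50. Below about AUC .70, error rate therefore hardly distinguishes a useful ranking from none. From .70 to .75 it falls by 0.72 points, and from .75 to .80 by 1.29 points.

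**3. Problem 1, unequal variances.** Non-event scores are N(0, 1) and event scores N(μ, s²), with one upper cut-off. AUC = Φ(μ/√(1+s²)).
- μ = 1.0, s = 0.7: AUC .794, lowest error 19.1%
- μ = 0.9, s = 2.0: AUC .656, lowest error 15.3%

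Error rate prefers the second model and AUC the first, so the ranking reverses.

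**4. Problem 8.** No event rate is stated, so a range is assumed, using the formulas of step 2.

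| Assumed event rate | AUC .75 | AUC .80 | Change |
|---|---|---|---|
| 10% | 9.91% | 9.60% | 0.30 points |
| 5% | 4.99% | 4.95% | 0.04 points |
| 3% | 3.00% | 2.99% | about 0.01 points |

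(Changes are taken before rounding.)

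**5. Sampling noise.** Candidates are scored on the same validation sample, so the relevant standard error is that of a paired difference. Simulation of the step 2 model, AUC .75 against .80, assuming score correlations of .6 to .8:

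| Setting (validation rows assumed) | Difference | Paired SE |
|---|---|---|
| 3%, 5000 rows | 0.01 | about 0.03 |
| 5%, 5000 rows | 0.04 | about 0.07 |
| 10%, 5000 rows | 0.30 | 0.17 to 0.19 |
| Problem 1, 1000 rows | 1.29 | 0.78 to 0.89 |

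The difference is below one standard error at 3% and 5%, and about 1.4 to 1.7 standard errors in the other two settings.

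**The case against.** The case on the other side has five parts.

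- **The term may be generic.** Aim 1 (a) says only error rate, and the article uses accuracy loosely for both AUC and R-squared. This is possible, but the only gloss, in Results, is classification error rate for the same method. If a generic sense is meant, the text needs to say so, because error rate has no ordinary meaning for a cost.
- **It is an outline of a draft.** The method is described as needing further work, and details sit in cited papers that are not shown. This stands against the reading, which a reader might infer, that the search cannot run on Problem 9 or is settled on the wrong objective. Applying Auto-ML to a cost outcome is planned, so some suitable loss is presumably intended. It does not remove the point: Techniques 1 and 4 are the planned improvements, and both keep error rate.
- **The rules work with any loss.** Technique 1's first threshold example is a rank and Technique 4 takes the best few, so both carry over. The example 5% margin does not carry over automatically.
- **The size can be overstated.** The .05 AUC margin for Problem 8 separates Auto-ML's model from an external comparator, not two candidates within the search, so the .75 to .80 step only illustrates sensitivity. Event rates, validation sizes and correlations in steps 4 and 5 are assumed. A standard error for a single error rate would overstate the noise, since candidates are paired. All of this stands.
- **The trial's comparisons are safe.** Final scoring uses the stated metric on held-out data, so a mismatched search could only work against Auto-ML and could not create a false success. Six of the seven benchmarks already match, and equal allocation would put about 25/7 = 3.6 researchers on Problem 1. Automatic selection is also part of what is being tested, so a failure it causes is still a genuine result. This stands and limits the consequence.

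**Conclusion.** The point holds as a mismatch between the stated search criterion and the stated metrics in Problems 1, 8 and 9. For Problem 1 the event rate is documented, and error rate is a weak guide to AUC at that rate: 18.9%, 18.2% and 16.9% at AUC .70, .75 and .80 under equal-variance binormal scores, with reversal possible otherwise. For Problem 8 the size depends on an event rate that the article does not give. For Problem 9 the criterion is undefined if error rate is read literally.

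A reader might go further and infer that the Aim 2 tests are invalid, or that error rate says almost nothing about the Problem 8 endpoint. The article supports neither: testing is on held-out data with the declared metric, and at an assumed 10% event rate error rate still carries some information. The consequence is a search that may be needlessly worse for Auto-ML in three of the nine problems, and a shortfall there that would be harder to attribute. It is worth correcting while the software is still being designed.

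**What to change.** In Aim 1 (a), Overview, and in Techniques 1 and 4, state that the search loss is the performance metric of the problem being solved:
- Problems 1 and 8: 1 minus AUC.
- Problem 9: 1 minus R-squared, or mean squared error.
- Problems 2-7: error rate, as now.

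Use that loss for the stage thresholds, for removing algorithms, for choosing the results to share, for the two-validation-sample comparison, and for the accuracy curve shown to the user. Re-express Technique 1's example 5% margin on the scale of each loss.

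The cost is a configurable loss function and slightly more computing per test. By the article's own account the design document is still being written, so the change can be made before the software is fixed.
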